## Abstract

**Background:**

Food insecurity is an important barrier to retention in care and adherence to antiretroviral therapy (ART) among people living with HIV infection (PLHIV). However, there is a lack of rigorous evidence about how to improve food security and HIV-related clinical outcomes. To address this gap, this randomized trial will evaluate three delivery models for short-term food and nutrition support for food insecure PLHIV in Shinyanga, Tanzania: nutrition assessment and counseling (NAC) alone**,** NAC plus food assistance, and NAC plus cash transfers.

**Methods/Design:**

At three HIV care and treatment sites, 788 participants will be randomized into one of three study arms in a 3:3:1 ratio, stratified by site: NAC plus food assistance, NAC plus cash transfer, and NAC only. Eligible participants are: 1) at least 18 years of age; 2) living with HIV infection; 3) initiated ART in the past 90 days; and 4) food insecure, as measured with the Household Hunger Scale. PLHIV who are severely malnourished (body mass index (BMI) < 16 kg/m^2^) will be excluded. Participants randomized to receive food or cash transfers are eligible to receive assistance for up to six months, conditional on attending regularly scheduled visits with their HIV care provider. Participants will be followed for 12 months: the initial 6-month intervention period and then for another 6 months post-intervention. The primary outcome is ART adherence measured with the medication possession ratio. Secondary outcomes include 1) retention in care; 2) nutritional indicators including changes in food security, BMI, and weight gain; 3) viral suppression and self-reported ART adherence; and 4) participation in the labor force.

**Discussion:**

This rigorously designed trial will inform policy decisions regarding supportive strategies for food insecure PLHIV in the early stages of treatment. The study will measure outcomes immediately after the period of support ends as well as 6 months later, providing information on the duration of the interventions’ effect. The comparison of food to cash transfers will better inform policies favoring cash assistance or will provide rationale for the continued investment in food and nutrition interventions for PLHIV.

**Trial registration:**

ClinicalTrials.gov: NCT01957917.

## Background

Although early initiation of antiretroviral therapy (ART) among people living with HIV/AIDS (PLHIV) has significant clinical benefits and can virtually eliminate onward HIV transmission [1, 2], these benefits hinge on retention in care and high levels of ART adherence. However, in sub-Saharan Africa, food insecurity, poor nutrition, and poverty are pervasive threats to ART’s potential effectiveness [3–6]. Food insecurity in particular is recognized as a barrier to ART initiation, retention in care, and adherence [7, 8], thus fostering interest in the potential for food and nutrition interventions to improve the health of PLHIV.

People are considered food secure when they have adequate physical, social, and economic access to sufficient, safe and nutritious food that meets their dietary needs and food preferences for an active and healthy life [9]. Studies have highlighted several pathways through which food insecurity impedes adherence to treatment and care in the general adult population of PLHIV [5]. First, the fear of increased hunger experienced or anticipated by people on treatment as well as the real or perceived fears of exacerbated side effects in the absence of adequate nutritional intake can reduce adherence to treatment recommendations. In addition, people who are food insecure might avoid or delay HIV treatment and care because of food insecurity’s overlap with household economic status and the real or perceived costs of ART or HIV primary care (e.g., transportation). Furthermore, food insecurity may influence ART adherence and care seeking through mental health pathways related to the anxiety and stress associated with hunger [10]. However, there is a paucity of rigorous evidence to guide initiatives for PLHIV, including which assistance modalities are best to improve food security, clinical outcomes, and household economic stability [11, 12].

### Interventions to improve food security

Some have hypothesized that nutritional support in the form of food baskets or food supplements may minimize or eliminate the food insecurity’s negative effects on adherence to treatment and care. To date, there have been four quasi-experimental studies examining the effect of such programs on ART adherence [13–16]. All were conducted in sub-Saharan Africa and compared food supplementation programs to clinics or regions not receiving the programs. Of these, three [13, 14, 16] found significant improvements in treatment adherence among food recipients. However, none of the studies had an experimental design and several evaluated food rations designed for the entire household [13, 14], which are likely to be cost prohibitive and/or unsustainable in resource-constrained settings.

In addition, there is ongoing debate about whether cash transfers can achieve the same nutritional and clinical goals as food assistance [17–21]. Studies conducted among people in the general population (not limited to PLHIV) suggest that although both food and cash transfers increase food consumption, food transfers result in *greater* increases in caloric intake than cash transfers, may be preferred by beneficiaries over cash, and may be more appropriate when food is scarce and/or food markets are functioning poorly [19, 20, 22, 23]. However, cash transfers give beneficiaries freedom of choice, may be cheaper to distribute and easier to monitor, and may be more “efficient” (under the assumptions of neoclassical microeconomic theory) than food transfers [19–21, 23, 24]. The growing body of evidence suggesting that financial incentives can be used to increase adherence to ART and retention in care bolsters the idea that cash transfers have the potential to strengthen the HIV care continuum, and might be equally, if not more, cost-effective than nutritional support for some health outcomes, such as ART adherence [25, 26]. However, there are limited data from resource-constrained settings about whether targeted cash assistance programs are effective for improving the health of PLHIV, and if so, their relative effectiveness when compared to other modes of support. The only randomized study to directly compare the effect of food and cash transfers among PLHIV on ART adherence found no difference in adherence between the two support strategies after 8 months in a sample of 293 clients in Zambia, although there was no comparison arm to determine the impact of the interventions over and above the standard of care [27].

### Rationale for the current study

To address this research gap, we designed a randomized study of three delivery models for short-term food and nutrition support for PLHIV in Tanzania who recently initiated treatment: nutrition assessment and counseling (NAC) alone**,** NAC plus food assistance, and NAC plus cash transfers. Participants in the two active treatment arms receiving food or cash transfers are eligible to receive assistance for up to six months, conditional on attending regularly scheduled visits with their HIV care provider.

The study focuses on ART initiates for several reasons. First, PLHIV who initiate ART with a low body mass index (BMI) have two to six times higher mortality rates than non-malnourished patients in the first years of treatment even after controlling for disease stage, and these individuals are also more likely to be lost to follow-up [28–30]. This suggests that food availability is especially critical among ART initiates [31]. Second, short-term food or cash support may provide a bridge until the participant’s health improves sufficiently to improve work productivity and hence earnings. This helps prevent households from having to sell productive assets in order to purchase food, especially if the HIV-infected household member is unable to work at the time of treatment initiation. In South Africa, there is a sharp decline in labor force participation in the year before PLHIV start treatment, followed by a slow but nearly complete re-entry into the workforce after treatment initiation [32]. Thus, by intervening at the time of ART initiation, household labor supply and productivity may rebound faster, preventing lengthy unemployment spells and/or preventing job loss entirely [12, 33]. This may also reduce deleterious spillover effects on nutrition, education, and other dimensions of household welfare [12].

A six-month support period for ART initiates was selected to be consistent with current policy and practice and for comparability to previous research [13]. For example, the World Food Programme commonly provides short-term assistance of 6–8 months duration for malnourished and/or food insecure PLHIV [12, 34], as does the widely recognized Academic Model for Prevention and Treatment of HIV/AIDS (AMPATH) in Kenya [34, 35]. Furthermore, lengthy periods of food or cash assistance are not likely to be feasible, affordable, nor sustainable in resource-constrained settings.

For these reasons, we hypothesized that short-term support among ART initiates may be an effective response during an important window of opportunity (ART initiation), when the risk of morbidity and mortality is high, good ART adherence habits are being formed, and household welfare is threatened. Our study will measure adherence to treatment and care immediately after the period of support ends as well as 6 months later, providing information on the duration of effect (if any).

### Primary objectives

Compare the effectiveness of a NAC plus food assistance program for food insecure PLHIV starting ART versus a NAC plus cash transfer program on ART adherence at 6 months.*Hypothesis*: NAC plus cash assistance will be non-inferior to NAC plus food assistance on ART adherence.Determine the effect of a nutrition assessment and counseling (NAC) program plus food or cash assistance for food insecure PLHIV starting ART versus NAC alone on ART adherence at 6 months.*Hypothesis*: Participants who receive NAC plus either food or cash transfers will have better adherence to ART than participants who receive NAC alone.

### Secondary objectives

The secondary objectives include evaluating the effectiveness of NAC plus food and cash transfers at 6 and 12 months of follow-up on: 1) retention in care; 2) nutritional indicators including changes in food security, BMI, and weight gain; 3) viral suppression and self-reported ART adherence; and 4) participation in the labor force.

## Methods

### Study setting and design

In Tanzania, 1,500,000 people are living with HIV infection and 399,886 are on ART [36]. The Global Hunger Index is 17.3, indicating serious levels of hunger [37]. The study is conducted in Shinyanga Region, a resource-poor region in the northwest “Lake Zone” of Tanzania where approximately 17 % of households have poor or borderline food consumption and HIV prevalence is 7.4 %, making this an ideal setting to examine how food and cash assistance may influence adherence to ART [38, 39].

We designed a 3-arm parallel group randomized trial to examine the effectiveness of short-term food and cash assistance added to the standard of care HIV services, including nutrition assessment and counseling (NAC). We include a standard-of-care comparison group that does not receive food or cash transfers. Participants will be recruited from 3 facilities,^1^ randomized to one of three study arms, and followed for 12 months: during the 6 month intervention period and then for another 6 months post-intervention. All sites participating in the study are currently trained in and implementing the President’s Emergency Plan for AIDS Relief (PEPFAR) Nutrition Assessment, Counseling, and Support (NACS) program [40].

### Inclusion and exclusion criteria

Eligible participants are: 1) at least 18 years of age; 2) living with HIV infection; 3) initiated ART in the ≤90 days; 4) food insecure, as measured with the Household Hunger Scale (score ≥2 indicating moderate to severe hunger in the household) [41, 42]; and 5) willing and able to provide written informed consent for the study. PLHIV who are severely malnourished (body mass index (BMI) < 16 kg/m^2^) are excluded from the study, as these individuals require therapeutic nutritional supplementation for nutritional recovery.

### Interventions

Participants are randomized to one of three study arms: NAC alone (comparison condition), NAC plus food assistance, and NAC plus cash transfers.NAC alone (comparison condition): Participants in the comparison arm receive the standard HIV primary care services available at HIV care and treatment clinics in Tanzania, including NAC.NAC plus food assistance: Participants in the NAC plus food assistance arm receive the standard of care services plus the opportunity to receive a monthly food basket for up to 6 consecutive months, conditional on attending their scheduled visits with their HIV care provider, which are typically monthly. The food basket consists of locally procured whole maize meal (12 kg), groundnuts (3 kg), and beans (3 kg). The composition of the food basket was determined with the input of experts in academic, government, and donor organizations and was selected to be applicable to other settings, not cost-prohibitive, and use foods available in the local markets. The food basket is intended to *supplement* the household’s food supply and is not intended to provide all of the required nutritional needs for all household members. Participants receive a targeted counseling message that “*this food is to help you stay healthy as you continue your HIV treatment, and you should use it to help you take your HIV medicine as your doctor has recommended.”* (A similar message is given to cash transfer recipients.) Food baskets (and cash transfers, described below) are distributed on the same two days per month for consistency.NAC plus cash transfer: Participants in the NAC plus cash transfer arm receive all of the standard of care services plus the opportunity to receive a monthly cash transfer for up to 6 consecutive months, conditional on attending scheduled visits with their HIV care provider. The cash transfer is 22,500 Tanzanian Shillings (approximately $11 USD) exclusive of transaction fees and is equivalently valued to the food basket. This value was selected to prevent undue coercion to study participants and to be consistent with the Tanzania Social Action Fund (TASAF), a government-run anti-poverty program which targets “orphans, disabled, elderly, widows/widowers, and those infected or affected by HIV/AIDS*,”* among other vulnerable groups [43]. TASAF provides $6-18 monthly to households depending on the presence and number of vulnerable children and elderly members. The transfer for this study, at ~ $11, is within this range, ensuring that the amount is policy-relevant. Cash is transferred to participants via a mobile money service (i.e., M-PESA) and transaction fees are paid by the research study. In the rare case that a participant does not have a cell phone, we will provide cash directly.

#### Conditionality

Participants in the food or cash assistance arms of the study are eligible to receive transfers for up to the first 6 consecutive months of the study, conditional on attending their scheduled visit with their HIV care provider. Trained research assistants consult the medical record to verify visit attendance. (In rare instances when visits are scheduled 60 or 90 days apart by the provider, participants receive the total value of 2 or 3 monthly transfers, respectively, if they attend the scheduled visit). After a detailed review of scheduling patterns, we developed a decision rule for eligible visits: transfers can only be made once every 26 days (to ensure that no one receives a transfer more than once every 4 weeks), and the actual visit must occur within a 4 day window (+/− 4 days) from the scheduled visit to encourage adherence to the physician’s recommended monitoring plan.

### Randomization

Participants are randomized into the food, cash, and comparison arms in a 3:3:1 ratio, stratified by site, using random permuted block sizes of 7, 14, and 21. Randomization procedures were conducted at the University of California, Berkeley and the procedures and group assignments were inaccessible to the local research team. Randomization assignments were listed in opaque sealed envelopes that were sequentially numbered. After participants provided written informed consent, trained research staff at study clinics selected the next envelope in numeric order and broke the seal to reveal the randomization assignment. Due to logistical considerations, participants and investigators were not blinded to intervention assignments.

### Data collection

A comprehensive in-person interview about individual and household characteristics, food security, ART adherence, and health service utilization will be conducted at baseline, 6 and 12 months along with quantification of plasma viral load. Visit attendance, CD4 count, pharmacy pick-up data, and other clinical and prognostic markers will be abstracted from medical and pharmacy records at 0, 6, and 12 months.

### Primary outcome

The primary outcome is ART adherence at 6 months, measured with the medication possession ratio (MPR), the proportion of time an individual is in possession of >1 ART dose or prescription for ART [44]. MPR is computed from pharmacy dispensing records as the number of days ARVs are prescribed or dispensed divided by the number of days in the interval, and has been shown to be associated with short-term virologic outcomes [44–47]. We will determine the proportion of patients with MPR ≥95 % (the 95 % cutpoint is based on prior studies [48]) during the 0–6 month interval (primary outcome).

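### Objective 2 reads a medication possession ratio as ART adherence although only the transfer arms are rewarded for attending visits; the conclusion should be stated as possession (refill adherence)

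*Protocol article*

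**What the plan says.** All references are to the protocol article.

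- **Transfer condition (Conditionality).** Food or cash is given "conditional on attending their scheduled visit with their HIV care provider". Timing matters too: "the actual visit must occur within a 4 day window". Checking is from clinic records: "Trained research assistants consult the medical record to verify visit attendance". The Interventions section describes these visits as typically monthly.
- **Comparison arm (Study setting and design).** "We include a standard-of-care comparison group that does not receive food or cash transfers".
- **Primary outcome.** "The primary outcome is ART adherence at 6 months, measured with the medication possession ratio (MPR". Possession is described as the share of time a person is "in possession of >1 ART dose or prescription for ART". The ratio is computed from pharmacy dispensing records as "the number of days ARVs are prescribed or dispensed divided by the number of days in the interval", then cut at 95 % over months 0 to 6. The support offered for it is a cited association with short-term virologic outcomes.
- **Objective 2 hypothesis (Primary objectives).** "Participants who receive NAC plus either food or cash transfers will have better adherence to ART than participants who receive NAC alone". The Analysis plan tests this on the same MPR outcome, pooling food and cash if they do not differ statistically.
- **Other measures (Data collection, Secondary outcomes).** Appointment adherence, viral suppression and self-reported adherence are secondary outcomes at 6 and 12 months. The Analysis plan does not link them to how the Objective 2 result is worded.

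**The concern.** In the transfers-versus-NAC contrast, one side receives a reward for turning up and the other does not. The primary outcome then counts something that is probably obtained by turning up. A refill collected under NAC alone and one collected under a transfer need not carry the same information about whether pills are taken, because the transfer arm has an added reason to attend. Even if MPR tracks virologic outcome well when visits are unrewarded, that relation may differ between the two sides of this contrast. The article does not discuss this.

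The prescription wording adds to it. If a prescription counts as possession, one written at a rewarded visit could raise MPR without any drug being handed over.

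What is at stake is the wording of the main claim over standard care. As written, an intervention that improved only attendance and supply could satisfy a hypothesis about taking ART.

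**Working it through.** **1. The plan's own sample sizes reproduce, so no arithmetic error is involved.**

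Objective 1: 75 % in both arms, margin 10 points, one-sided alpha 0.025, power 80 %.
n = (1.960 + 0.842)² × 2 × 0.75 × 0.25 / 0.10² = 294.3, rounded up to 295, as stated.

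Objective 2: 60 % v 75 %, alpha 0.05, allocation 6:1 (from 3:3:1 with food and cash pooled). Two-sided testing and 80 % power are my assumptions, since neither is stated for this objective.
- Pooled proportion = (0.60 + 6 × 0.75) / 7 = 0.729.
- The usual two-proportion formula gives 85 in NAC, or 93 with continuity correction.
- 93 / 0.85 = 109.4, rounded up to 110, as stated. Total: 2 × 339 + 110 = 788.

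**2. Power for the planned Objective 2 shift.**

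After 15 % loss: 110 × 0.85 = 93.5 (about 94) and 678 × 0.85 = 576.3 (about 576).
- SE = √(0.60 × 0.40 / 94 + 0.75 × 0.25 / 576) = 0.0537.
- Power (unpooled Wald) = Φ(0.15 / 0.0537 − 1.96) = about 80 %. With the pooled-variance test it is about 84 %.

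This holds whatever produces the shift.

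**3. How much attendance alone could move MPR ≥95 %.**

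Assumptions not in the article: a 180-day interval; 30-day refills obtained only at attended visits; a missed refill not made up; visits independent with equal probability of attendance. The cut tolerates 0.05 × 180 = 9 uncovered days, so one missed refill fails it. Then P(MPR ≥95 %) = aᵐ, where a is per-visit attendance and m the number of refill visits.

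| m | a for 60 % | a for 75 % | Rise |
|---|---|---|---|
| 5 | 0.60^(1/5) = 90.3 % | 0.75^(1/5) = 94.4 % | 4.1 points |
| 6 | 0.60^(1/6) = 91.8 % | 0.75^(1/6) = 95.3 % | 3.5 points |

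Under these assumptions a small gain in attendance yields the full planned effect with pill-taking unchanged. Buffer stock or late refills within the 9-day tolerance would alter the figures.

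**4. Would requiring a viral-suppression result be a sound remedy?**

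At 94 v 576, with suppression rates assumed:

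| Suppression, NAC v transfers | SE | Power |
|---|---|---|
| 70 % v 70 % | – | 2.5 % (chance of favouring transfers) |
| 70 % v 80 % | 0.0501 | 51 % |
| 70 % v 85 % | 0.0496 | 86 % |

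The last row needs suppression to rise by as much as MPR ≥95 % does. Suppose instead that suppression follows MPR class and the 60 % to 75 % gain is wholly genuine:
- 85 % suppressed above the cut, 60 % below: NAC 0.60 × 0.85 + 0.40 × 0.60 = 75.0 %; transfers 0.75 × 0.85 + 0.25 × 0.60 = 78.8 %. SE 0.0478, power 12 %.
- 90 % above, 50 % below: NAC 74.0 %; transfers 80.0 %. SE 0.0482, power 24 %.

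On these assumptions the requirement would withhold the adherence wording in at least three-quarters of trials with a real effect. Gains in suppression within MPR class would raise these powers.

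**The case against.** **The link from visit to refill is inferred.** The article does not say that drug is collected at the visit that earns the transfer. Visit attendance and pharmacy pick-up are listed as separate data items, and MPR is computed from dispensing records. The transfer depends on seeing the provider, not on a refill. This stands, and it limits the point to what may happen. Typically monthly visits and the prescription wording make the link likely.

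**Attendance is part of the intervention.** Conditionality is designed in openly, and the Background names the costs of care as a route from food insecurity to poor adherence. Drug that is not possessed cannot be taken. This also stands: better supply is a real benefit, and MPR is a reasonable primary outcome. It does not make supply the same as ingestion.

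**The checks are already collected.** Viral suppression, self-report and appointment adherence are measured in all arms, and the Discussion concedes that the exact pathways will not be known. A refill-only result would therefore be visible to a careful reader. That lowers the seriousness, but the Objective 2 hypothesis is still worded as adherence and tested on MPR alone.

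**A stronger reading is tempting:** that a positive Objective 2 result would be bought attendance and nothing more, mislabelled in about 80 % of trials. The documents do not support it. That figure is simply the power of the MPR test, and it becomes a rate of false labelling only if none of a 15-point gain involves added pill-taking. Nothing in the article implies that.

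**Conclusion.** The point holds as one of interpretation. Rewarded attendance on one side of Objective 2, combined with an outcome counting days prescribed or dispensed, means that a higher proportion with MPR ≥95 % shows more ART possession. It does not by itself show more pill-taking. Part of any difference may be attendance; how large a part cannot be derived from the article. The illustration (3.5 to 4 points of attendance for the whole planned shift) shows only that the 95 % cut is sensitive to attendance, and it rests on the assumed refill pattern.

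A reader might also infer that the adherence claim should depend on a significant viral-suppression difference. That does not follow. Such a rule would act as a second primary outcome for which the 110-person NAC arm was not sized, with power of about 12 % to 24 % when suppression follows MPR class as assumed above.

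Objective 1 is less affected, because food and cash carry the same visit condition.

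**What to change.** 1. **Primary outcome:** count only dispensed drug. Remove the prescription alternative from both the definition of possession and the computation of the ratio.
2. **Analysis plan, Objective 2:** keep the MPR ≥95 % test as primary, but state its conclusion as an effect on ART possession (refill adherence), and align the wording of the Objective 2 hypothesis.
3. **Reporting:** beside the MPR result, give the 6-month differences in viral suppression and self-reported adherence, with 95 % confidence intervals, in the same pooled contrast. Treat them as supportive evidence, with no requirement that either be significant.

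The cost is a narrower headline claim. Viral load, self-report and pharmacy records are already collected, so no new data are needed, and the sample size and primary test are unchanged.
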